#### Collective efficacy

CE is a latent construct comprised the structural and cognitive components that facilitate a community's shared belief in its ability to come together and execute actions related to a common goal.^21^ A review of the literature and established conceptual frameworks will be performed to define the CE construct. A sequential exploratory mixed qualitative and quantitative design will be used to develop and refine a scale to measure CE and test hypotheses. Field workers will administer the refined, multi-item, Likert-type CE scale to one randomly selected household member aged 18 years or older in each household in round 3.

#### Women's empowerment

Four dimensions of women's empowerment will be measured in rounds 3 and 4: group participation, leadership, decision-making and freedom of movement. Group participation and leadership will be measured using modules from the Women's Empowerment in Agriculture Index (WEAI), which has been tested in South Asia.^74^ Decision-making will be measured using questions from the women's status module of Demographic and Health Surveys. Freedom of movement will be measured using questions from the project-level Women's Empowerment in Agriculture Index (pro-WEAI). These measures will be collected for the primary female caregiver of the youngest child <5 years of age and were selected based on the importance of women's empowerment for child nutrition.^75^
^76^ Women's empowerment is conceptualised as an outcome and a potential mediator along the pathway between the Gram Vikas intervention and child health outcomes.

#### Menstrual hygiene management

Menstrual hygiene management practices vary worldwide and depend on personal preference, socioeconomic status, local traditions and beliefs and access to water and sanitation resources.^77^ Unhygienic washing practices are common in rural India and among women and girls in lower socioeconomic groups and may increase risk of urogenital infection.^78–80^ However, the link between access to water and sanitation, menstrual hygiene management and urogenital infections has been poorly studied. Household surveys will be administered in round 4 to a randomly selected woman aged 18 or older, in a subset of 800 households, and will capture self-reported urogenital infection, defined as at least one of the following symptoms: (1) abnormal vaginal discharge (unusual texture and colour/more abundant than normal), (2) burning or itching in the genitalia, (3) burning or itching when urinating or (4) genital sores.^79^

#### Sanitation insecurity

This study will assess the associations between sanitation access and sanitation insecurity with mental health among women. In a previous research in Odisha, a contextually specific definition and measure for sanitation insecurity was developed, with associations between facets of sanitation insecurity and mental health independent of sanitation facility access.^81^ This previously developed measure will be used to determine if levels of sanitation insecurity differ between intervention and control villages and how it may be associated with mental health outcomes, specifically well-being, anxiety, depression and distress. Household surveys will be administered in round 4 to a randomly selected woman aged 18 or older, in a random subset of 800 households.

#### Fecal sludge management

In sanitation systems where sewerage is not feasible, such as the household toilets constructed as part of the MANTRA intervention, safe management of fecal waste is necessary. Although there is growing emphasis on safe fecal sludge management (FSM), research has mainly focused on urban settings.^82^
^83^ Preliminary research in Odisha suggests that FSM in this rural setting is a substantial challenge and may impact household use of toilets. In round 3, household surveys and spot checks of toilets in intervention villages will be used to assess toilet use and FSM practices.

## Statistical analyses

The effect of the intervention on infrastructure coverage, access, and use (aim 1), and the effect of the intervention on improving health (aim 3), will be analysed using logistic, linear, log binomial or negative binomial multilevel regression depending on the outcome, to compare intervention versus control villages. Prevalence of FSM practices in intervention communities will be assessed using multilevel regression (aim 1). For all models, the hierarchical structure of the data will be accounted for using random effects. Estimation of relative risks through Poisson regression or binary regression methods for binary outcomes will be considered to ensure robustness of results. Mediation of the potential association between intervention and nutritional status outcomes by women's empowerment will be assessed using multilevel structural equation modelling, and statistical approaches to reduce bias will be explored as needed.^84^

The impact of intervention on reducing environmental fecal contamination (aim 2) will be assessed through two methods. First, hierarchical logistic and negative binomial multilevel regression to estimate intervention effects on the relative scale will be used to compare intervention versus control villages. Estimation of relative risks through Poisson regression or binary regression methods for binary outcomes will be considered to ensure robustness of results. Second, a stochastic microbial risk framework will be used to assess differential fecal environmental contamination between intervention and control villages.

The cost and cost-effectiveness of the intervention (aim 4) will be assessed in two steps. Incremental intervention benefits will be ascertained by combining health benefit data, from analysis of health outcome data and established averted cost data, with other averted social opportunity costs. An incremental cost-effectiveness ratio, expressed in cost per disease-specific DALY, will be calculated by dividing the incremental intervention costs by the incremental intervention benefits.

The CE scale will be analysed using a psychometric approach in which factor analytics are employed to identify an appropriate factor solution and test the reliability and validity of the CE scores. Once a CE factor solution and an empirically derived multilevel data structure have been identified, the association between CE and intervention effectiveness will be analysed using multilevel generalised linear mixed models to estimate relative risks,^85^
^86^ (aim 5). For all outcomes, variables used in the matching process may be considered as covariates, as needed, in addition to individual, household and community-level risk factors. Covariates that are statistically associated with outcomes of interest in bivariate analyses will be considered for inclusion in final multivariable models, following standard stepwise model-building approaches. Secondary analyses may also evaluate models for effect modification as relevant, including exposure-mediator interaction for mediation models and cross-level interaction, by assessing changes in parameter values based on potential effect modifiers. Potential effect modifiers may include breastfeeding for seroconversion outcomes, and climate factors and population density for environmental fecal contamination and health outcomes. However, this study was not designed to assess effect modification and therefore is not specifically powered for these analyses. For all outcomes, unadjusted models will be presented along with models adjusting for covariates.

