#### Matching

After restriction, genetic matching was used to match potential control villages to the randomly selected intervention villages without replacement.^5^
^40^
^41^ Villages were exact matched on district to limit any political or large-scale geographic variation between district populations and were also matched on preintervention demographic, socioeconomic, sanitation and water access characteristics listed in table 1.^5^ These village-level matching variables were selected due to their theorised association with the primary outcome, diarrhoeal diseases, as well as data availability.

**Table 1 BMJOPEN2016012719TB1:** Preintervention characteristics used in matching, and balance diagnostics before and after matching and exclusion process

	Intervention	Control (all eligible)	Std diff (all eligible)	Control (study)	Std diff (study)
Variable	(n=45)	(n=1580)		(n=45)	
Number of households	157.9	215.5	0.37	148.1	0.06
Population <6 years (%)	16.2	16.9	0.19	16.3	0.02
Household income score (x̅)	2.9	3.1**	0.26	2.9	0.01
Household goods owned (x̅)	1.1	1.2*	0.27	1.1	0.02
Pucca house (%)	59.2	61.6	0.09	60.5	0.05
≥2 meals a day (%)	57.7	63.7	0.19	57.8	0.01
Scheduled caste (%)	11.5	18.7**	0.46	11.8	0.01
Scheduled tribe (%)	33.4	19.1*	0.31	29.8	0.08
Female literacy (%)	30.9	29.8	0.07	30.9	0.00
Open defecation (%)	95.6	95.2*	0.04	95.8	0.01
Improved drinking water source† (%)	38.6	42.5	0.10	37.2	0.02
Water source <500 m and 50 m elevation (%)	81.5	72.2	0.31	81.7	0.01

All eligible: all villages that are eligible for the matching process after restriction.

Std diff (absolute standardised difference): a value >0.1 is considered meaningful imbalance.^42^

Kolmogorov-Smirnov bootstrap p values: *<0.05, **<0.01.

†Ganjam villages only; no data available for Gajapati villages.

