#### Exclusion

The field team visited matched potential control villages and intervention villages to assess suitability for the study through a rapid assessment interview with village leadership and to ensure accessibility. Villages were excluded if they are not within 3 hours travel of the field office in Brahmapur, had sustained major infrastructure damage due to a natural disaster, or if there was a current or planned sanitation or water intervention by an organisation external to the village in the next 12 months as determined through the rapid assessment interview with village leadership. In addition, villages were excluded if there were fewer than three households with children <5 years old. As villages were removed from the pool of prospective control villages, the matching process was repeated for all intervention villages and remaining eligible control villages, and balance measures were assessed. The matching and exclusion processes were repeated as necessary.

After the iterative matching and exclusion process was complete, covariate balance was assessed for all matching variables for the final set of intervention and control villages through examination of balance measures.^42–44^ Matching resulted in an improvement in balance as assessed through comparison of several measures including q-q plots, Kolmogorov-Smirnov bootstrap p values and standardised differences. After matching, there were no significant differences between the intervention and control groups (table 1).

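### The plan matches villages on district and on predictors of diarrhoea but does not commit to using these factors in the models; they enter only if data-driven selection keeps them

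*Protocol article*

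**What the plan says.** On design, the Matching section of the protocol article states that "genetic matching was used to match potential control villages to the randomly selected intervention villages without replacement", and that "Villages were exact matched on district to limit any political or large-scale geographic variation between district populations". Villages were also matched on the twelve pre-intervention variables in Table 1. The same section says these were chosen because they were thought to be associated with diarrhoea and because data were available.

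On analysis, the Statistical analyses section uses multilevel regression "to compare intervention versus control villages" and states: "For all models, the hierarchical structure of the data will be accounted for using random effects". The levels are not listed, and neither district nor the matched pair is named. For covariates, the rule for all outcomes is that "variables used in the matching process may be considered as covariates, as needed", next to individual, household and community risk factors. It continues: "Covariates that are statistically associated with outcomes of interest in bivariate analyses will be considered for inclusion in final multivariable models", by stepwise model building. Finally, "unadjusted models will be presented along with models adjusting for covariates".

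**The concern.** The article gives a reason, fixed before the data, for regarding the matching variables as prognostic, and it made district the one factor matched exactly. The covariate rule then treats these factors like any other candidate: they may enter as needed, and screening against the outcome guides what is kept. Two things are at stake.

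- **Pre-specification.** The adjusted model for the primary outcome is not fixed. Whether a design factor is in it can turn on a p-value.
- **Precision.** Variance between villages is a large part of the error of a village-level comparison. If district and the matching variables explain some of it and are left out, that share stays in the error term. The standard error is then larger than the design allows.

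**Working it through.** **Inputs from the Sample size section.** Seven-day prevalence 8.8%; village variance 0.07; household variance 0.57; four rounds; 45 villages per arm; 26 households per village; 10% loss, so 26 × 0.9 = 23.4 households.

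**Assumptions.** The effect size of 0.20 is read as a risk ratio of 0.80, so the intervention prevalence is 0.8 × 0.088 = 0.0704. The test is two-sided at 0.05, with one child per household. The share *f* of village variance explained by district and the matching variables is not in the documents and is shown as a range.

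**Effect.** ln(0.088/0.912) − ln(0.0704/0.9296) = −2.3383 + 2.5806 = 0.242.

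**Formula.** Var(log OR) = sum over arms of [(1/(4p(1−p)) + 0.57)/H + 0.07(1−f)] / 45; power = Φ(0.242/SE − 1.96).

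- Control arm: 1/(4 × 0.088 × 0.912) = 3.115; adding 0.57 gives 3.685.
- Intervention arm: 1/(4 × 0.0704 × 0.9296) = 3.820; adding 0.57 gives 4.390.
- Sum 8.075; divided by H this is 0.3106 (H = 26) or 0.3451 (H = 23.4).
- Village part: 2 × 0.07 × (1−f) = 0.14(1−f).

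**The plan's own figure first (f = 0).** The SE is √((0.3106 + 0.14)/45) = 0.100 and power is 68% at 26 households, or 65% at 23.4. The plan states at least 80%. Other readings come close to that or reach it: a one-sided test gives 78% at 26 households, and treating 0.07 and 0.57 as standard deviations gives 80% at 23.4. Effect scale, sidedness and children per household are not fully stated, so this mismatch does not show that the sample size is wrong. The present point does not rest on it.

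**Effect of using the matching factors.**

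| Share f explained | SE, 26 households | Power, 26 | Power, 23.4 |
|---|---|---|---|
| 0 | 0.100 | 68% | 65% |
| 25% | 0.096 | 71% | 68% |
| 50% | 0.092 | 75% | 71% |
| 75% | 0.088 | 79% | 75% |

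The village part is 0.14/0.4506 = 31% of the variance at 26 households and 0.14/0.4851 = 29% at 23.4, which caps the gain. Even if all of it were explained, power would be 83% or 79%. If 0.07 and 0.57 are standard deviations, the largest possible gain is about 1.5% in the SE and one point of power.

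**Strict pairing, for comparison.** At 23.4 households, a t-test with 88 degrees of freedom and no pairing has power 63.6%. A paired test with 44 has 62.6, 63.9, 65.9 and 69.4% at within-pair correlations of 0, 0.1, 0.25 and 0.5. Break-even is at about 0.08; below that, pairing costs power.

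**Validity.** Village proportions were simulated (4,000 runs, 23 households per village) and analysed without pairing. Type I error was 4.9, 3.1 and 1.8% at within-pair correlations of 0, 0.5 and 1. Ignoring effective matching is conservative, not anti-conservative.

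**The case against.** The strongest reply is that this is a condensed article. The random-effect levels are commonly left to a fuller plan, the matching variables are permitted as covariates, and adjusted models are promised. That stands against reading the text as saying that the matching is ignored: the plan does not commit to using it, which is a weaker statement. It does not answer the covariate rule, which the article sets out affirmatively as optional entry with data-driven selection.

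A second reply is that matching did its work on confounding when villages were selected, so an unpaired comparison is legitimate. This stands. District is balanced between arms by construction, so its role in the model is precision, not removal of bias.

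Third, the pairs may not be the natural unit. Matching was repeated as controls dropped out, and "covariate balance was assessed for all matching variables for the final set of intervention and control villages"; closeness within pairs was not the stated criterion. The sample size claims no gain from pairing either. This stands, and it makes a compulsory pair term debatable.

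A reader might infer more from three other figures, which the documents do not support:

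- Scheduled tribe at 33.4% against 29.8% has a standardised difference of 0.08, below the article's own threshold of 0.1. The rule also permits adjustment for it.
- Sanitation access of over 23% against 8% in the two districts dates from 2008. The matching data are from 2001 and 2002, so this is not a baseline difference. It lies between districts, not between arms.
- The fix should not be presented as restoring 80% power. The shortfall itself is not established, and no share up to 75% reaches 80% in the table.

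**Conclusion.** The point holds as one of pre-specification and, conditionally, of efficiency. The article exact matches on district and matches on variables it regards as prognostic, then leaves their use to need and stepwise selection. The analysis is not invalid: it is at most conservative.

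The gain from fixing the rule is about 3, 7 or 11 points of power if 25, 50 or 75% of the village variance is explained, and about nil if little is. These sizes rest on the reading of 0.20 as a risk ratio of 0.80, on 0.07 and 0.57 being variances on the log-odds scale, and on a normal approximation that ignores degrees of freedom spent on covariates. The share explained is an assumption without a source in the documents. The case for fixing the rule in advance does not depend on it.

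**What to change.** In the covariate paragraph of Statistical analyses, state that district (fixed effect) and the Table 1 matching variables with complete data enter the adjusted intervention-versus-control models for primary and secondary outcomes, exempt from bivariate screening and stepwise selection. Improved drinking water source needs its own rule, because Table 1 has no data for Gajapati: use it only within Ganjam, or state how the missing district is handled. A plain complete-case fit would drop that district. Report a model with a matched-pair random intercept as a sensitivity analysis, and keep the unadjusted models as planned.

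The change is a sentence or two of model specification, using district and matching data that already exist. If the eleven other Table 1 variables each enter as one linear term, the cost with district is 12 village-level degrees of freedom, leaving 88 − 12 = 76 of the 88 available from 90 villages. The pair model also needs the final pairing to have been recorded, which the article does not state.

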### Study design

This study uses a matched cohort design to assess the effectiveness of a completed intervention with data collected across four study rounds from June 2015 to October 2016 (figure 2). Data were collected in all study rounds for diarrhoea, acute respiratory infection, nutritional status and stored and source water outcomes to assess seasonality. Data were collected in rounds 2 and 4 for EED, seroconversion, and hand-rinses, and cross-sectionally in one or more rounds for the remaining outcomes. As described below, control villages were matched to randomly selected intervention villages through a multistep restriction, genetic matching and exclusion process using the following eligibility criteria.

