### Eligibility criteria for villages

#### Restriction

Intervention villages were randomly selected from a list of Gram Vikas villages in Ganjam and Gajapati districts provided by the non-governmental organization (NGO), after restriction to villages with a Motivation phase start date between 2002 and 2006 and a Construction phase start date no earlier than 2003. Since the intervention process takes on average 3 years, the criteria for the Motivation start date helped to identify those villages with ongoing interventions at the same time. In addition, this allowed the use of the Government of India Census 2001 and the BPL Survey 2002 data to characterise baseline characteristics used in the matching process in intervention and control villages.

Eligible control villages include all villages without a Gram Vikas intervention within the study districts which: (1) are not within the same Gram Panchayat (a political subdivision with some administrative responsibility for water and sanitation comprised several villages) as a Gram Vikas village, or bordering a Gram Vikas village, and (2) had not received a Motivation visit from the Gram Vikas NGO. These criteria serve to limit the possibility of previous partial exposure to the intervention through spill over from adjacent villages or direct contact with the NGO. These criteria also increase the strength of the comparison provided by the control villages, that is, it increases the likelihood that if they had received a motivation visit from Gram Vikas, the control villages would have been equally as likely as the intervention villages to demand the intervention.

In addition, to be eligible for inclusion intervention and control villages must (1) appear in the Government of India Census 2001 and the BPL Survey 2002, (2) have a population of at least 20 households and (3) be within ∼3 hours travel from the study office in Brahmapur, Ganjam District. This last criterion is due to logistical constraints.

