### Outcome measurement

Outcomes, and individual, household, and community-level risk factors, will be measured through surveys, interviews or through the collection and analysis of environmental, stool or dried blood spot samples. All survey questions will be translated into the primary local language, Odia, and back-translated to confirm wording. Household surveys include household and individual factors and will be verbally administered by trained field workers to the mother or primary caregiver of the youngest child <5 in each household, unless otherwise specified below. Community surveys will be verbally administered to the *sarpanch* (village head) or any other member of village leadership. Survey data will be collected on mobile phones using Open Data Kit.^47^ GPS coordinates for households, water sources and other relevant sites will be collected using Garmin eTrex 10 or 20 devices (Garmin, Olathe, Kansas, USA).

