## Discussion

This matched cohort study is one of the first to evaluate the effect of a rural combined household-level piped water and sanitation intervention, implemented at the community level, on a large scale. The matched design provides a rigorous means for estimating causal effects given that randomisation to the intervention group was not feasible due to the several year implementation process.^5^ By focusing on an intervention where the implementation process is complete, it also limits the risk presented by randomised controlled trials, where the intervention has little uptake, an especially important study challenge given the interdependence of exposure and outcomes within communities, and a problem that has characterised previous trials of sanitation interventions in India.^15^
^16^

A strength of this study is the assessment of health impacts using the holistic WHO definition of health, including not just disease status, and also mental, social and physical well-being.^87^ Outcomes along the causal chain include standard, but more subjective measures, such as reported diarrhoeal diseases and respiratory infection, as well as more objective measures such as fecal environmental contamination, soil-transmitted helminth infection and anthropometry. Although there is risk of response bias for reported outcomes, it is unlikely to be differential by intervention status since the study team is not directly linked to Gram Vikas. Even though field workers may be aware of village intervention status, laboratory staff analysing water, hand rinse, stool and blood samples will be blinded. In addition, this study includes the more novel use of seroconversion for enteric pathogens, biomarkers of EED and measures of CE in an evaluation assessment. While there are limitations inherent to observational studies, the matched study design and multivariable modelling analysis plan reduce the potential for confounding. However, there is still the potential for residual unmeasured confounding.

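### Covariates for the adjusted models are chosen by association with the outcome and stepwise building, from a pool that does not exclude variables the intervention may have changed, so the adjusted effects may be biased

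*Protocol article*

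**What the plan says.** The Statistical analyses section gives one covariate rule for all outcomes. The pool is described thus: "variables used in the matching process may be considered as covariates, as needed, in addition to individual, household and community-level risk factors". The route into the model is a screen on the outcome: "Covariates that are statistically associated with outcomes of interest in bivariate analyses will be considered for inclusion in final multivariable models". The same sentence then names a stepwise procedure for building the model. The section gives no selection threshold and no candidate list, and it does not exclude variables that the intervention could have altered. It does commit to showing an unadjusted model beside each adjusted one, but names neither as primary.

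Three other places fix the timing:
- Outcome measurement: "Outcomes, and individual, household, and community-level risk factors, will be measured through surveys, interviews", that is, during the study.
- Study design: "data collected across four study rounds from June 2015 to October 2016".
- Eligibility criteria for villages (Restriction): intervention villages had a "Motivation phase start date between 2002 and 2006", and the same paragraph adds "Since the intervention process takes on average 3 years".

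The Discussion gives the adjusted model a role in the causal argument: "the matched study design and multivariable modelling analysis plan reduce the potential for confounding".

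**The concern.** The stated objective is the effectiveness of the combined programme, which is a total effect. A model for a total effect in a non-randomised study should adjust for what preceded the intervention or could not be changed by it, and should leave out what the intervention itself altered.

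The rule does not make that distinction. Some risk factors recorded in 2015-16, such as a child's age, cannot be consequences of the programme. Others can. Toilet and water access and use, hand-washing stations and disposal of child feces are recorded in every round, and the protocol itself describes women's empowerment as a possible mediator.

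Screening on association with the outcome makes this worse. A variable that carries much of the effect is associated with the outcome for that very reason and tends to pass. A theory-chosen confounder with a modest association may fail, and the matching variables have no guaranteed place. Stepwise building then reports standard errors as if the model had been fixed in advance. If adjusted and unadjusted results disagree, the protocol does not say which one answers the primary question.

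**Working it through.** The plan gives no figure of its own on covariate adjustment, so there is none to reproduce. The check covers timing, then the size and direction of the possible bias.

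**1. Timing.** Starts in 2002 to 2006 plus about 3 years give average completion in 2005 to 2009. Against rounds from June 2015 to October 2016:
- completion in 2005: about 10 to 11 years before measurement;
- completion in 2009: about 6 to 7 years before measurement.

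Counted from the start, the gap is about 9 to 14 years. Apart from the matching variables, the candidates measured by the study therefore all postdate the intervention.

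**2. Simple formula.** If a share s of the log effect passes through adjusted mediators and the true ratio is 0.80, the adjusted ratio is 0.80^(1-s). This gives 0.80^0.75 = 0.846, 0.80^0.5 = 0.894, 0.80^0.25 = 0.946 and 0.80^0 = 1.000 for s = 0.25, 0.5, 0.75 and 1.

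**3. Simulation of the screen.** Inputs from the Sample size section: 45 villages per arm, 26 households less 10% (26 x 0.9 = 23.4, run as 23), four rounds, and variances 0.07 (village) and 0.57 (household). The effect size of 0.20 has no stated scale and is read as a true odds ratio of 0.80.

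Assumptions not in the documents: one binary variable M measured after the intervention, with prevalence 30% in control and 85% in intervention villages; M enters if its bivariate p<0.05; logistic models with village-robust standard errors; 200 runs per scenario.

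| Share of effect through M | M selected | Mean OR, unadjusted | Mean OR, final model | p<0.05, unadjusted | p<0.05, final |
|---|---|---|---|---|---|
| 0 | 23% | 0.81 | 0.82 | 54.5% | 49% |
| 0.25 | 51% | 0.81 | 0.85 | 52% | 30.5% |
| 0.50 | 75.5% | 0.82 | 0.90 | 51.5% | 13.5% |
| 0.75 | 94.5% | 0.80 | 0.94 | 59% | 9.5% |
| 1 | 98.5% | 0.81 | 1.00 | 56.5% | 6% |

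With 200 runs, a proportion near 50% has a Monte Carlo standard error of sqrt(0.25/200) = 3.5 points. The final-model odds ratios agree closely with step 2. The more of the effect M carries, the more often the screen selects it. If M is never admitted, the estimate stays at about 0.80 to 0.83 in every scenario.

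The unadjusted share of about 52% to 59% should not be set against the stated 80% power, because the plan states neither the effect scale nor one- or two-sided testing. A normal approximation gives 57-64% for a two-sided test at OR 0.80, 68-78% two-sided at RR 0.80, and 78-81% one-sided at RR 0.80. Only the fall within each row bears on this point.

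**4. Direction.** Keep s = 0.5 and add an unmeasured cause shared by M and diarrhoea:
- If it raises both, adjusting for M gives OR 0.74, away from the null. The screen selected M in only 9% of runs, so the mean final OR was 0.80.
- If it raises M and lowers diarrhoea, M is always selected and the OR is 1.11, past the null.

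The simulation covers the bivariate screen with one variable. It does not quantify the effect of stepwise building on the standard errors.

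**The case against.** A reader might infer that the adjusted models will condition on mediators and so will be pulled toward the null. The documents do not support that certainty. Covariates are only to be considered, and no mediator is named as one. The protocol treats the obvious candidates as outcomes or as subjects of separate analyses: WASH access and use under aim 1, fecal contamination under aim 2, collective efficacy under aim 5, and women's empowerment in its own mediation model. The authors plainly knew of the causal chain. The direction is not certain either, as step 4 shows.

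The safeguards are real. Every outcome also gets an unadjusted estimate, which is free of mediator adjustment. In Table 1 every standardised difference after matching is 0.08 or lower against the cited threshold of 0.1, and district was matched exactly, so losing a matching variable would probably matter little. The Discussion credits the matched design as well as the modelling, so the causal claim does not rest on the adjusted model alone. Covariate sets may also properly differ between outcomes.

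All of this stands and narrows the point. It does not remove it. Treating a variable as an outcome in one analysis does not keep it out of the covariate pool of another, and no exclusion is written. Nor is this detail left to an unseen analysis plan: the selection method is stated, and the stated method is the problem.

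**Conclusion.** The point holds in limited form. The stated rule is data-driven, draws on variables measured years after the intervention without excluding those it may have affected, and makes the pre-intervention matching variables optional. The adjusted estimates may condition on mediators, may omit confounders, and will have standard errors that take no account of the selection.

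The size depends on a mediated share that the documents do not give. Under the assumptions above, a true odds ratio of 0.80 becomes on average 0.85 in the final model at a quarter mediated, 0.90 at a half and 1.00 if all is mediated. It stays close to 0.80 if none is. Toward the null is the most likely direction, not an assured one. The understatement of the standard errors has not been quantified.

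The unadjusted models and the matched balance limit the damage. They do not settle which estimate answers the primary objective, because no model is named primary.

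**What to change.** Replace the screening and stepwise rule before analysis:

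- **Adjustment set.** For total-effect models of the health outcomes, pre-specify district, the Table 1 pre-intervention variables available in both districts, study round, and child age and sex where applicable. Add any outcome-specific covariates that the intervention cannot change.
- **Primary model.** State which model is primary, and keep presenting the unadjusted models.
- **Intermediate variables.** Keep WASH access, use and practices, environmental contamination, women's empowerment and collective efficacy out of total-effect models. Use them only in the mediation or other named analyses.
- **Improved drinking water source.** Handle it separately, for example by omitting it or using it only in a Ganjam sensitivity analysis. The Table 1 footnote says that it is lacking for Gajapati, so a complete-case model containing it would drop every village in that district.

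The change is to wording and needs no new data. The statistical cost is about a dozen village-level degrees of freedom out of 90 villages: Table 1 lists 12 variables, less the water-source variable leaves 11, and district makes 12.
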